**Methods and design:**

In this prospective, single-center, observational investigation of PoPH patients with chronic liver disease, a targeted 2,500 Japanese adult patients regularly visiting Shinshu University Hospital in Matsumoto, Japan, for chronic liver disease will complete a standardized questionnaire on the presence of PoPH symptoms. If the respondent has signs of possible PoPH, ultrasound echocardiography (UCG) will be performed as a primary screening. In the case that UCG findings indicate pulmonary hypertension, the patient will be referred to a cardiologist for further evaluation, whereby a definitive diagnosis PoPH can be made. PoPH prevalence and etiology will be investigated at the time of diagnosis. Afterwards, patients with PoPH will be followed for five years for determination of survival rate.

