## Materials and methods

This is an ongoing, prospective, single-center, observational study that will run from October 1, 2020 to October 30, 2027. The study flowchart is presented in Fig 1. This study was reviewed and approved by the Institutional Review Board of Shinshu University School of Medicine (approval number: 4891) on September 29th, 2020. Written informed consent will be obtained from all subjects. The study is being conducted according to the principals of the Declaration of Helsinki.

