### Trial design and follow-up

Participant registration for the study will run from October 1, 2020 to October 30, 2022. All participants will answer the written questionnaire described in Table 2 in the outpatient clinic of Shinshu University Hospital. If at least one question is positive, informed consent will be obtained from the individual for enrollment in the study. Then, the participant will undergo ultrasound echocardiography (UCG) as a first-line screening. If the participant exhibits UCG-positive findings indicating a high probability of PoPH as shown in Tables 3 and 4, the patient will be referred to a cardiologist in the Department of Cardiology for further evaluation, whereby a definitive diagnosis will be made by right heart catherization findings as shown in Table 5. The frequency of PoPH patients will be analyzed (Observational study 1) along with the etiology of PoPH in chronic liver disease (Observational study 2).

**Table 2 pone.0249435.t002:** Standardized questionnaire on symptoms suggesting portopulmonary hypertension (translated from Japanese; respondents indicate “yes” or “no”).

1) Do you feel you cannot work comparably to other people of the same age and gender?
2) Do you feel you cannot move as fast as other people do?
3) Do you feel you cannot move at the same pace as others?
4) Do you need rest when climbing stairs or carrying heavy loads?
5) Do you ever experience shortness of breath?
6) Do you ever experience faintness?
7) Do you ever experience tiredness and/or persistent malaise?
8) Do you ever experience dizziness and/or vertigo?
9) Do you ever experience facial edema and/or pretibial edema?

**Table 3 pone.0249435.t003:** Echocardiographic probability of PAH in patients having symptoms indicative of PAH [21].

Peak tricuspid regurgitation velocity (m/s)	Presence of other echo PH signs	Echocardiographic probability of PAH
≤2.8	No	Low
≤2.8	Yes	Intermediate
2.9–3.4	No	
2.9–3.4	Yes	High
>3.4	Not required	

Abbreviations: PAH, pulmonary artery hypertension; PH, pulmonary hypertension.

**Table 4 pone.0249435.t004:** Echocardiographic signs suggesting PAH used to assess the probability of PAH in addition to tricuspid regurgitation velocity measurement in Table 3 [21].

A: Ventricles	B: Pulmonary artery	C: Inferior vena cava and right atrium

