Right ventricle:left ventricle basal diameter ratio >1.0	Right ventricular outflow doppler acceleration time <105 msec and/or midsystolic notching	Inferior cava diameter >21 mm with decreased inspiratory collapse (<50% with a sniff or <20% with quiet inspiration)
Flattening of the interventricular septum (left ventricular eccentricity index >1.1 in systole and/or diastole)	Early diastolic pulmonary regurgitation velocity >2.2 m/sec	Right atrium area (end-systole) >18 cm^2^
	Pulmonary artery diameter >25 mm	

Abbreviations: PAH, pulmonary artery hypertension.

**Table 5 pone.0249435.t005:** Diagnosis criteria of PoPH [21–23].

1. Existence of PAH by right heart catheraization
a. Mean pulmonary artery pressure (mPAP) ≥ 25mmHg
b. Pulmonary artery wedge pressure (PAWP) ≤ 15mmHg
2. Existence of portal hypertension
Hepatic vein pressure gradient (HVPG) ≥ 5mmHg
3. Rule out of other etiology of PAH

Abbreviations: PoPH, portopulmonary hypertension; PAH, pulmonary artery hypertension.

When a PoPH diagnosis is made, the following clinical data will be collected: etiology of liver disease, age, gender, height, body weight, history of medication, drinking habit, smoking habit, New York Heart Association (NYHA) classification, 6-minute walking distance, FibroScan^®^ results, blood and urine data, thoracic-abdominal enhanced computed tomography findings, right heart catheter findings (mean pulmonary artery pressure, right atrial pressure, pulmonary artery wedge pressure, cardiac index, cardiac output, pulmonary vascular resistance, and mixed venous oxygen saturation), and echocardiographic findings.

Upon diagnosis, PoPH treatment will be initiated by a cardiologist based on the guidelines for pulmonary hypertension issued by the Japanese Circulation Society [22]. Patients will be evaluated every six months for blood and urine findings, abdominal ultrasonography results, and clinical symptoms. UCG will be performed on a yearly basis. The observation period will be five years from the time of patient enrollment and will end if the patient dies or becomes lost to follow-up. Ultimately, the 5-year survival rate of PoPH patients and factors associated with survival will be analyzed (Observational study 3).

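### The 5-year survival endpoint has two conflicting starting points: enrollment (consent, before echocardiography) in the follow-up section and PoPH diagnosis in the abstract

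*Protocol article*

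**What the plan says.** All places are in the Protocol article.

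- **Enrollment.** Trial design and follow-up: after a positive questionnaire answer, "informed consent will be obtained from the individual for enrollment in the study".
- **Next steps.** Same section: "Then, the participant will undergo ultrasound echocardiography (UCG) as a first-line screening". Patients with suggestive findings go to cardiology, where "a definitive diagnosis will be made by right heart catherization findings as shown in Table 5".
- **Length of observation.** Same section: "The observation period will be five years from the time of patient enrollment".
- **Survival population.** Same section: "the 5-year survival rate of PoPH patients and factors associated with survival will be analyzed". This group can be identified only after catheterization.
- **Abstract, Methods and design.** After a sentence on what is examined at diagnosis: "Afterwards, patients with PoPH will be followed for five years for determination of survival rate".
- **Calendar.** "Participant registration for the study will run from October 1, 2020 to October 30, 2022" (Trial design and follow-up). The study "will run from October 1, 2020 to October 30, 2027" (Materials and methods).
- **Analysis.** Statistical analysis names Kaplan-Meier and stepwise Cox regression, and no time origin.

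**The concern.** A survival rate needs one starting event, and that event should be the one that brings patients into the cohort. Here entry is the catheter diagnosis, but the written follow-up rule starts earlier, at consent.

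- **Clock at enrollment.** A patient who dies between consent and catheterization is never classed as PoPH. Every patient who is counted therefore carries a period in which death could not be recorded, and the error can only raise estimated survival. The Cox model is affected too: catheter findings, NYHA class and walking distance are collected at diagnosis, and treatment starts then, so they would be measured after time zero.
- **Clock at diagnosis, follow-up window as written.** Observation ends five years after consent, so each patient has five years minus their own diagnostic gap.

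At stake is the secondary endpoint (Endpoints, Observational study 3). Prevalence and etiology, the primary endpoint, are not affected.

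**Working it through.** **1. Which clock does the calendar follow?** Last registration 30 October 2022 + 5 years = 30 October 2027, the stated study end, with no days to spare. The calendar fits the enrollment clock. A patient diagnosed after 30 October 2022 cannot have five years from diagnosis before the study ends.

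**2. How many patients does that limit?** Registration lasts 25 months (1 October 2020 to 30 October 2022). Assuming uniform accrual and a common gap:
- gap of 3 months: 22/25 = 88% have room for five years from diagnosis;
- gap of 6 months: 19/25 = 76%.

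**3. Size of the effect.** Inputs:
- *Gap g*: not stated. The only evidence is in the Discussion: one PoPH case was diagnosed within about the first two months of screening, so that one gap was at most about two months. I take 1 to 6 months as the working range and show 12 months as an extreme.
- *True 5-year survival from diagnosis, S5*: 14%, which the Discussion cites for untreated patients, and 50%, which is my assumption.
- *Hazard*: constant (assumption), λ = −ln(S5)/5. This gives −ln(0.14)/5 = 0.393 per year and −ln(0.50)/5 = 0.139 per year.

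Formulas: longest follow-up from diagnosis = 5 − g. Estimate at five years on an enrollment clock without delayed entry = exp(−λ(5 − g)).

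| Gap | Longest follow-up from diagnosis (years) | Estimate if true value is 14% | Estimate if true value is 50% |
|---|---|---|---|
| 1 month | 4.92 | 14.5% (+0.5) | 50.6% (+0.6) |
| 2 months | 4.83 | 14.9% (+0.9) | 51.2% (+1.2) |
| 3 months | 4.75 | 15.4% (+1.4) | 51.8% (+1.8) |
| 6 months | 4.50 | 17.0% (+3.0) | 53.6% (+3.6) |
| 12 months | 4.00 | 20.7% (+6.7) | 57.4% (+7.4) |

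Example, 6 months: exp(−0.393 × 4.5) = 0.170.

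**4. Comparison with sampling error.** Expected PoPH cases among the target of 2,500:
- at the pilot 1/300 (Discussion): 2,500/300 = 8.3;
- at 1% to 2%, the figure the Introduction cites for cirrhosis: 25 to 50.

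The pilot rate is probably low, because only 36 of the 153 symptomatic patients had echocardiography. The standard error √(S5(1 − S5)/n), ignoring censoring, is:
- at S5 = 50%: 17.3 points with 8.3 cases, 10.0 with 25, 7.1 with 50;
- at S5 = 14%: 12.0, 6.9 and 4.9 points.

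At a 6-month gap with 50 cases, the bias is 3.6/7.1 = 0.5 of a standard error at 50% survival and 3.0/4.9 = 0.6 at 14%. With fewer cases or shorter gaps the fraction is smaller.

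**The case against.** **The observation period is not the Kaplan-Meier origin.** The follow-up section says how long patients are watched, not when the survival clock starts. An article may leave the origin to an analysis plan that is not shown. This stands in part: the silence of the Statistical analysis section is not the finding. The finding is that two stated follow-up rules disagree, and an analysis plan cannot recover follow-up that the protocol does not collect.

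**The abstract already gives five years from diagnosis.** True, and the calendar allows it for most patients. A reader might infer that 5-year survival from diagnosis is never observed, or that nobody is at risk at year five. The documents do not support that. It follows only if the enrollment-based window is combined with a diagnosis clock, and no section states that combination. Patients diagnosed by 30 October 2022 fit in the present calendar.

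**The numbers rest on assumptions.** This stands. No gap is given, and the single pilot case points to a short one, although one early case does not bound later ones. The 14% concerns untreated patients, whereas here treatment starts at diagnosis, so it illustrates a high hazard and is not a forecast.

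**Deaths before diagnosis.** A reader might also count these as damage that the fix repairs. At the 14% hazard and a gap of 3 to 6 months they would be 1 − exp(−0.393 × 0.25) = 9.4% to 1 − exp(−0.393 × 0.5) = 17.8% of such patients. They are missing from any cohort defined by diagnosis, including the corrected one, so they are not part of the bias that the fix removes.

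**Conclusion.** The inconsistency is certain: the follow-up section and the abstract start the five years at different events, and the calendar matches the enrollment clock. On that clock survival is biased upward. On a diagnosis clock within the same window, follow-up falls short of five years by each patient's gap. Both consequences hold for any non-zero gap.

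The size is modest: about 0.5 to 3.6 points for gaps of 1 to 6 months, and about 1 point at two months. This assumes a constant hazard, a common gap, and true survival of 14% or 50%. The standard error is roughly 7 to 17 points at 50% survival and 5 to 12 at 14%. Only a work-up of about a year would bring the bias close to, or above, the smallest of these. The point deserves correction because the stated rules conflict and the correction is cheap. The documents do not show that the bias dominates the result or that the endpoint cannot be observed.

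**What to change.** 1. Use one origin in the abstract, in Trial design and follow-up, and in Statistical analysis: time zero for Kaplan-Meier and Cox is the date of the diagnostic right heart catheterization. Cox covariates are then measured at time zero.
2. Reword the observation period for PoPH patients to five years from diagnosis.
3. For patients diagnosed after 30 October 2022, either censor at study end, which Kaplan-Meier handles, or extend the vital-status check beyond 30 October 2027 by the diagnostic gap. State which.
4. If the enrollment clock is kept, let patients enter the risk set at diagnosis (delayed entry). This removes the immortal time without changing the calendar. The curve is then survival from enrollment among those who reached diagnosis, with few patients at risk early on, so with this few cases the diagnosis origin is simpler.
5. Record both dates and report the distribution of the gap, so that readers can judge its effect.

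Cost: wording changes and, at most, a short extension of vital-status follow-up for the last enrollees. If censoring is chosen instead, the estimate at five years is somewhat less precise.

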#### Diagnosis of clinical stage

Liver cirrhosis will be diagnosed by histologic examination and/or characteristic clinical signs of advanced liver disease. Hepatocellular carcinoma will be determined by histologic examination, blood test, and/or imaging studies.

#### Endpoints

The primary endpoint in this study is the prevalence of PoPH in Japanese patients with chronic liver disease and its etiology (Observational study 1 and study 2). The secondary endpoint is the overall 5-year survival rate (Observational study 3).

### Safety

Since this study is observational, there are no direct risks associated with participation.

### Statistical considerations

#### Sample size estimation

As the exact prevalence of PoPH remains unknown, we planned to screen all patients regularly visiting our department for chronic liver disease observation or treatment. Approximately 4,800 patients visit our department yearly in addition to 300 new patient referrals. Symptoms indicating PoPH have been found in roughly half of patients with chronic liver disease in the outpatient questionnaire. Assuming that 20% of patients will decline informed consent, we aim to recruit 2,500 cases with chronic liver disease.

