## Discussion

This prospective observational study aims to clarify the clinical characteristics of PoPH in the Japanese population. Both cirrhosis and non-cirrhosis stage patients may become complicated with PoPH. Although the frequency of PoPH in patients with cirrhosis has been described, PoPH prevalence in chronic liver disease remains unknown. Unlike in cohorts from Western countries, where the proportion of ALD is high [24], viral hepatitis-related chronic liver disease is more prevalent in Japan. In the few studies on PoPH in Asia and Japan investigating disease prevalence and incidence, AIH and PBC were found to be more likely complicated with PoPH [5]. However, due to the small number of cases included in those investigations, the clinical picture of PoPH is uncertain. The present study will seek to answer these important questions.

A retrospective study from the United States showed that patients untreated for PoPH had a poor 5-year survival rate of 14%, which was associated with the delayed diagnosis of PoPH [25]. One reason could be that up to 60% of patients with PoPH were asymptomatic [1]. PoPH cases are contraindicated for liver transplantation due to high operative mortality and poor prognosis. Early intervention for PoPH is therefore essential to overcome this issue and improve prognosis. An established standardized questionnaire may be helpful in PoPH screening as a first diagnostic step.

During the past two months, this study’s questionnaire has been administered to 300 patients with chronic liver disease meeting the inclusion criteria. Interestingly, 153 patients (51.0%) described symptoms suggestive of PoPH. Among them, 36 patients providing informed consent underwent further UCG analysis. Two cases were found to have PAH, while one case was diagnosed as having PoPH. As previously reported, the prevalence of PoPH is expected to be very low. By recruiting a sufficient number of patients, however, we aim to determine the actual status of PoPH in Japan.

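### The recruitment target of 2,500 does not follow from its stated inputs, which give about 2,040, and the Abstract attaches the same number to a different group

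*Protocol article*

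**What the plan says.** Sample size estimation (protocol article) gives a feasibility count; no power or precision target is stated. Its inputs are:

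- Patient pool: "Approximately 4,800 patients visit our department yearly in addition to 300 new patient referrals".
- Symptom rate: "Symptoms indicating PoPH have been found in roughly half of patients with chronic liver disease in the outpatient questionnaire".
- Consent and target: "Assuming that 20% of patients will decline informed consent, we aim to recruit 2,500 cases with chronic liver disease".

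Trial design and follow-up fixes the order of events: questionnaire first, consent and enrolment if at least one answer is positive, then echocardiography (UCG). It also gives the window: "Participant registration for the study will run from October 1, 2020 to October 30, 2022".

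The Abstract (Methods and design) speaks of "a targeted 2,500 Japanese adult patients regularly visiting Shinshu University Hospital" and makes these the people who fill in the questionnaire. Target population repeats 2,500 as a total of regularly attending patients and does not mention symptoms or consent.

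The Discussion reports early experience: "During the past two months, this study’s questionnaire has been administered to 300 patients with chronic liver disease meeting the inclusion criteria". Of these, "153 patients (51.0%) described symptoms suggestive of PoPH", and then: "Among them, 36 patients providing informed consent underwent further UCG analysis".

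**The concern.** The sentence that states the 20% refusal is the one that states the target, yet the target looks like the symptomatic pool before any refusal. The same 2,500 also appears at two different stages of the funnel: people answering the questionnaire, and people recruited after a positive questionnaire and consent. The factor between those stages is 0.5 × 0.8 = 0.4, so the two meanings differ 2.5-fold.

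This is the only sample-size figure in the document. The Discussion relies on recruiting enough patients to establish the status of a rare condition. With no precision target stated, a reader can judge sufficiency only from this number, so it should be derivable and have one meaning.

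**Working it through.** **Inputs.** From Sample size estimation: 4,800 yearly patients, 300 referrals, about 0.5 symptomatic, 20% declining. From Trial design and follow-up: registration from October 2020 to the end of October 2022, about 25 months. From the Discussion: 300 questionnaires in two months, 153 positive, 36 with consent and UCG.

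**Step 1: try to reproduce 2,500.** Recruited = pool × symptomatic share × (1 − refusal).

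| Reading | Calculation | Result |
|---|---|---|
| All stated inputs, one year | 5,100 × 0.5 × 0.8 | 2,040 |
| Observed 51% symptomatic | 5,100 × 0.51 × 0.8 | 2,081 |
| Existing patients only | 4,800 × 0.5 × 0.8 | 1,920 |
| Two years of referrals | (4,800 + 600) × 0.5 × 0.8 | 2,160 |
| Two full years, all distinct patients | 10,200 × 0.5 × 0.8 | 4,080 |
| Refusal not applied | 5,100 × 0.5 | 2,550 |
| Refusal not applied, 4,800 at 51% | 4,800 × 0.51 | 2,448 |

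No row that applies the refusal gives 2,500. The closest matches are the last two, which leave it out. Reaching 2,500 with both factors needs 2,500 / 0.4 = 6,250 distinct patients. The shortfall of 2,040 is (2,500 − 2,040) / 2,500 = 18%; that of 2,160 is 14%.

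**Step 2: the Abstract's meaning.** If 2,500 people complete the questionnaire, enrolled = 2,500 × 0.5 × 0.8 = 1,000.

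**Step 3: what the early data suggest.**

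- Questionnaire pace: 300 / 2 = 150 per month; over 25 months, 3,750.
- At that pace with the assumed 80% consent: 3,750 × 0.5 × 0.8 = 1,500, which is 40% below 2,500.
- Observed uptake to date: 36 / 153 = 23.5% (exact 95% CI 17.1% to 31.1%); per questionnaire, 36 / 300 = 12%.
- If that yield persisted: 3,750 × 0.12 = 450, or 5,100 × 0.12 = 612 if the whole pool were given the questionnaire.

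**Step 4: effect on precision.** The documents give no expected rate for this population, so take 1% among those enrolled purely as an illustration. The exact 95% CI is 0.65% to 1.47% with 25 cases in 2,500, and 0.60% to 1.51% with 20 in 2,040. These are practically the same.

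**The case against.** **Patient turnover.** The 4,800 is a yearly figure and registration lasts about 25 months. The number of distinct patients over that time is not given. Between no turnover beyond referrals (5,400 patients, 2,160 recruited) and complete turnover (10,200 patients, 4,080 recruited) there is room for 2,500. This is arithmetically possible, but nothing in the text supports 6,250 distinct patients. The population is described as regular attenders, with new patients listed separately at 300.

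**The Abstract is condensed.** Enrolled patients also complete the questionnaire, so its sentence could be compatible with 2,500 enrolled. However, its next sentence sends respondents to UCG only if they have suggestive signs. That places the 2,500 before symptom selection. The wording is at best ambiguous.

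**The early data.** A reader might infer that the 36 of 153 disproves the 80% consent assumption and that the study will screen only 450 to 610 patients. The document does not support that. The 36 are patients who had both consented and undergone UCG after two months. The text does not say how many of the other 117 were asked, declined or were waiting. The confidence interval of 17% to 31% covers sampling error only, not pending patients. The 25-month projection also assumes a constant pace, which is nowhere stated. This part of the objection stands.

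**Consequence.** A reader might also infer that the primary estimate loses much of its precision. Step 4 shows that the arithmetic slip alone does not cause this, and no stated precision target is missed. This too stands.

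**Conclusion.** The stated target is not reconciled with its inputs. Applied in the order the protocol sets out, they give 2,040, or 2,160 with two years of referrals, against 2,500: an overstatement equal to 14% to 18% of the target. The likeliest explanation is that the 20% refusal was stated but not applied, or that 2,500 is really the number of symptomatic patients to be approached. The Abstract's use of 2,500 would imply about 1,000 enrolled.

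These conclusions use only the planning figures and assume that the yearly pool is largely the same people returning. The early data add a caution: 1,500 rests on an unchanged questionnaire pace, and 450 to 610 rests in addition on uptake staying at 24%. The latter is a low scenario, not a forecast.

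This is an error in the stated figure and its labelling. It is worth correcting because it is the document's only sample size, but it changes no analysis and by itself has little effect on precision.

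**What to change.** 1. In Sample size estimation, either restate the recruited target as about 2,040 (or 2,160, saying which period is counted), or keep 2,500 and label it as symptomatic patients to be approached for consent.
2. Give 2,500 one meaning in the Abstract, Target population and Sample size estimation.
3. Report the uptake so far (36 of 153, consent and UCG combined, after two months) beside the 80% assumption. If a projection of 450 to 610 is given, label it as a low scenario and say that some patients may have been pending.

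This changes wording only. No extra enrolment is asked for and no analysis changes; the cost is a less favourable stated figure.
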